## Abstract

**Introduction:**

The large reservoir of tuberculosis (TB) infections is one of the main reasons for the persistent incidence of TB. Accurate diagnostic tests are crucial to correctly identify and treat people with TB infection, which is vital to eliminate TB globally. The rdESAT-6 and rCFP-10 (Cy-Tb) injection (‘Cy-Tb’), a TB-specific antigen skin test and STANDARD F TB-Feron FIA (‘Standard F TB’) measuring interferon-gamma by fluorescence immunoassay assay are two novel tools for the diagnosis of TB infection which offer advantages compared with current tests in low-resource settings and reduced costs to both health systems and TB-affected people. The proposed study aims to evaluate the diagnostic accuracy of these two new tests for TB infection diagnosis.

**Methods and analysis:**

This cross-sectional study aims to assess the diagnostic accuracy for TB infection of the Cy-Tb skin test and Standard F TB assay (investigational tests) compared with the QuantiFERON-TB Gold Plus (QFT-Plus) assay as the immunological reference standard. Three different cohorts of study participants will be recruited at the Vietnam National Lung Hospital: adults with bacteriologically confirmed pulmonary TB (n=100), household contacts of people with TB (n=200) and people without TB infection (n=50). All consenting participants will undergo simultaneous testing with Cy-Tb, Standard F TB and QFT-Plus. The primary endpoint is the diagnostic accuracy of the Cy-Tb skin test and Standard F TB assay, expressed as sensitivity and specificity against the reference standard.

**Ethics and dissemination:**

Ethical approval was granted by the Vietnam National Lung Hospital Institutional Review Board (65/23/CN-HDDD-BVPTU) and the Swedish Ethical Review Authority (Dnr 2023-04271-01). Study results will be disseminated to the scientific community and policymakers through scientific publications.

**Trial registration number:**

NCT06221735.

STRENGTHS AND LIMITATIONS OF THIS STUDYThis is the first study to compare the accuracy of STANDARD F TB-Feron FIA (Standard F TB) versus QuantiFERON TB Gold Plus (QFT-Plus) as well as the first study to simultaneously compare both Cy-Tb and Standard F TB to QFT-Plus.The study will be conducted in one of the 30 countries with the highest tuberculosis (TB) burden in the world, where the tests have not been evaluated before, ensuring the feasibility of recruiting an adequate number of participants.All study tests will be quality assured as they will be conducted at the leading microbiological laboratory in Vietnam, the Vietnam National Reference Lab.A limitation is that the reference standard used in the study (QFT-Plus assay) also has suboptimal sensitivity, but is currently the best available test for the diagnosis of TB infection and is recommended by the WHO.A limitation of the study is its sole performance in one setting, where participants are homogeneous concerning genetic polymorphism.

## Introduction

### Background

 Tuberculosis (TB) is an infectious disease that is a leading cause of morbidity and mortality globally. There were an estimated 1.3 million total deaths caused by TB in 2022.^1^ Vietnam is one of the 30 highest TB burden countries, with an estimated 172 000 persons developing TB (including people living with HIV) in 2022.^2^

TB infection continues to be a significant cause of the increasing number of overall infections. After exposure to *Mycobacterium tuberculosis* (MTB), 5%–10% of people with TB infection will develop active TB, usually within the first 2 years after exposure.^3^ In 2018, the WHO estimated the global prevalence of TB infection to be 23%, meaning approximately 1.7 billion people were infected worldwide.^4 5^ A recent re-estimation using mathematical modelling demonstrated that in order to end TB by 2050, at least one-quarter of the global population living with TB infection would require TB preventive therapy.^6^

The tuberculin skin test (TST) and interferon-gamma (IFN-γ) release assays (IGRA) are currently the two preferred diagnostic tools for detecting TB infection. TST uses Tuberculin PPD RT 23 intradermally, which is affordable and easily performed.^7^ TST is currently the most frequently used TB infection test in Vietnam. However, TST has low sensitivity and specificity, particularly in people who are immunocompromised or have been BCG vaccinated, and people must return to a health facility to have the induration on their arm interpreted. IGRAs are more expensive and technically more complex, requiring phlebotomy, trained staff and laboratory equipment. Neither method is ideal for accurate and prompt diagnosis of TB infection in a community setting.^8^ Therefore, it is critical to develop new test methods to achieve the public health goal of preventing progression from TB infection to active TB and thereby reducing transmission.

Cy-Tb (Serum Institute of India, Pune, India) is an *M. tuberculosis* antigen-based skin test that was endorsed by the WHO in 2022.^9^ The test uses *M. tuberculosis*-specific antigens (rdESAT-6 and rCFP-10), which are injected intradermally, providing results after 48–72 hours, similar to the TST. However, a recent study indicated the superior performance of Cy-Tb compared with TST, with results in line with the QuantiFERON-TB Gold Plus (QFT-Plus) assay (QIAGEN, Venlo, The Netherlands).^10^

Simplified versions of IGRAs are emerging,^11^ including the lateral flow Standard F TB assay (SD Biosensor, Gyeonggi-do, Republic of Korea). Standard F TB has fewer manual processing steps than current-generation IGRAs. After incubation for 16–24 hours, the results will be available in 15 min. Following the stimulation with ESAT-6 and CFP-10 antigens, the IFN-γ production in whole blood is measured by a fluorescent immunoassay.^12^ A recent clinical trial comparing the sensitivity and specificity of the Standard F TB versus QIAreach QuantiFERON-TB (QIAGEN, Venlo, The Netherlands), using TST as a reference standard, showed that the Standard F TB has 88.9% sensitivity and 92.5% specificity for TB infection diagnosis.^13^ However, given the limited accuracy of TST in diagnosing TB infections, further studies comparing to the current gold standard are warranted. Compared with QFT-Plus, the Standard F TB assay may offer important advantages, such as being able to be implemented in low-resource settings, and reducing the financial burden on health systems and people with TB. The Standard F TB assay is currently undergoing Expert Review Panel for Diagnostics and WHO review.^14^

Currently, there are no studies comparing the accuracy of Standard F TB versus QFT-Plus. In addition, there are also no head-to-head comparisons of the sensitivity and specificity of Cy-Tb and Standard F TB. The studies comparing the accuracy of Cy-Tb test versus QFT-Plus have been conducted in Spain and South Africa,^9 15^ whereas there are no studies in a high TB burden, Asian population. This study was designed to address these knowledge gaps.

### Aims

#### Main objective

The main objective is to evaluate the accuracy of the Cy-Tb skin test and the Standard F TB assay versus the QFT-Plus assay as diagnostic methods of TB infection in Vietnam, a high TB burden setting.

#### Specific objectives

*Objective 1*: to verify the sensitivity of Cy-Tb and Standard F TB for TB infection diagnosis among adults with microbiologically confirmed pulmonary TB, using QFT-Plus test as a reference standard.

*Objective 2*: to evaluate the specificity and sensitivity of the Cy-Tb and Standard F TB tests, compared with QFT-Plus for TB infection diagnosis.

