### Study population

For objective 1, the study will enrol 100 eligible participants with microbiologically confirmed pulmonary TB at the National Lung Hospital, Hanoi, Vietnam for the purpose of verifying the sensitivity of (1) Cy-Tb and (2) Standard F TB for TB infection diagnosis. For objective 2, to evaluate the sensitivity and specificity of the Cy-Tb and Standard F TB tests for TB infection diagnosis, the study will recruit 250 eligible participants, including 200 household contacts of people with pulmonary TB and 50 people with known negative IGRA tests who report no history of exposure to TB.

*Group 1*: people with microbiologically confirmed pulmonary TB. The sensitivity of the Cy-Tb test and Standard F TB assay to diagnose TB infection will be confirmed in this group.

*Group 2*: household contacts of persons with bacteriologically confirmed, pulmonary TB. The sensitivity and specificity of the Cy-Tb test and Standard F TB assay to diagnose TB infection will be verified in this group.

*Group 3*: persons with known negative IGRA tests among those at low risk of TB infection. The specificity of Cy-Tb and Standard F TB for TB infection testing will be estimated using this group.

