#### Endpoints

*Primaryendpoint*: point estimate of sensitivity with 95% CI of the Cy-Tb test and Standard F TB assay.

*Secondaryendpoint*: point estimates of sensitivity and specificity with 95% CI of the Cy-Tb test and Standard F TB assay.

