### Data analysis plan

Points estimates of sensitivity and specificity with 95% CI will be calculated based on Wilson score methods to accommodate for the loss of coverage in small samples. The Cy-Tb and Standard F TB test index accuracy will be evaluated to fit with the case definition and results compared with the QFT-Plus reference standard test results presented in table 1.

**Table 1 T1:** The case definition and results

	Definitions			
Test results		Tuberculosis infection	Not infected	Total
	Detected	True positive	False positive	True positive+false positive
	Not detected	False negative	True negative	False negative+true negative
	Total	True positive+false negative	False positive+true negative	Total

Concordant with the methods employed in a systematic review by WHO, we consider the rate of negative results to represent proxy specificity regardless of TB incidence and estimates.^20^ Differences in proportion of negative results between investigated tests and the reference test will be calculated. In addition, we will also calculate the rate of negative results on the Cy-Tb and Standard F TB tests among QFT-Plus negative participants.

Sensitivity is the percentage of participants with positive study tests among those with microbiologically confirmed TB (group 1).

Specificity is the percentage of participants with negative study tests among those at low risk for TB infection (group 3). We will also calculate the proportion of people with negative index tests among those at risk for TB infection (group 2).

The descriptive statistics will be calculated for the sample and the contingency table will be created to evaluate the diagnostic performance, including sensitivity, specificity and associated 95% CI for the Cy-Tb test and Standard F TB assay in comparison with the reference standard. The area under the curves, that is, areas under the receiver-operating characteristics curve will be calculated to estimate the comparative diagnostic accuracy of the Cy-Tb test and Standard F TB assay and QFT-Plus.

Multiple multivariate logistic regression models will be performed to adjust for confounders while analysing associations between participants characteristics and test accuracy. Subgroup analysis of test accuracy in different groups will be done with regard to gender, age, BMI, comorbidities, TB exposure, etc.

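### Group 1 sensitivity is set against two different reference standards, and the abstract and Endpoints section name different primary measures, so the primary estimate is not uniquely fixed

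*Protocol article*

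**What the plan says.** On the reference standard for sensitivity:

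- Specific objectives, Objective 1: sensitivity of Cy-Tb and Standard F TB is to be verified "among adults with microbiologically confirmed pulmonary TB, using QFT-Plus test as a reference standard".
- Abstract, Methods and analysis: both tests are "compared with the QuantiFERON-TB Gold Plus (QFT-Plus) assay as the immunological reference standard".
- Data analysis plan, definition: "Sensitivity is the percentage of participants with positive study tests among those with microbiologically confirmed TB (group 1"). QFT-Plus plays no part in it.
- Data analysis plan, paragraph introducing Table 1: index test "results compared with the QFT-Plus reference standard test results presented in table 1".
- Study population, Group 2 (household contacts): "The sensitivity and specificity of the Cy-Tb test and Standard F TB assay to diagnose TB infection will be verified in this group". These participants have no microbiological standard, so QFT-Plus is implied.

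On which measure is primary:

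- Abstract: diagnostic accuracy, "expressed as sensitivity and specificity against the reference standard".
- Endpoints, primary: "point estimate of sensitivity with 95% CI of the Cy-Tb test and Standard F TB assay".
- Endpoints, secondary: "point estimates of sensitivity and specificity with 95% CI of the Cy-Tb test and Standard F TB assay".

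Neither entry in the Endpoints section names a group or a reference standard.

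**The concern.** Under Objective 1 the denominator in Group 1 is the patients who are QFT-Plus positive. Under the Data analysis plan it is every confirmed patient. The two coincide only if QFT-Plus is positive in all of Group 1. The article does not expect that: its limitations list and its Significance section both concede that QFT-Plus has less than ideal sensitivity.

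The Endpoints section does not settle the matter. Three quantities fit its primary entry: Group 1 against microbiology, Group 1 against QFT-Plus, and Group 2 against QFT-Plus. The abstract adds specificity. At stake is whether the headline sensitivity is fixed before the data are seen or can be picked afterwards from several defensible readings.

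**Working it through.** **Which definition does the sample size follow?** Inputs from the Sample size section: assumed sensitivity 75.8% (Cy-Tb) and 88.9% (Standard F TB), precision 0.10, 95% CI, 10% dropout. Formula: n = 1.96² × p(1 − p) / 0.10².

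- Cy-Tb: 3.8416 × 0.758 × 0.242 / 0.01 = 70.47, rounded up to 71.
- Standard F TB: 3.8416 × 0.889 × 0.111 / 0.01 = 37.91, rounded up to 38.

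These are the stated Group 1 figures. They treat every Group 1 patient as infected, because any QFT-Plus positivity factor below 1 would push them above 71 and 38. Group 2, by contrast, is divided by the 50% assumed infected and by 0.9 for dropout: 71 / 0.5 / 0.9 = 157.8, giving 158; 38 / 0.5 / 0.9 = 84.4, giving 85. So the Group 1 sizing agrees with the Data analysis plan, and the clause in Objective 1 is the outlier. (The Group 1 figures also omit the stated 10% dropout. With it they would be 70.47 / 0.9, giving 79, and 37.91 / 0.9, giving 43. That is a separate point and has no practical effect with 100 enrolled.)

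**How far apart can the two definitions be?** Let Se be the proportion of all Group 1 patients positive on the index test and q the proportion positive on QFT-Plus. The article gives no q, so a range is assumed. Sensitivity among QFT-Plus positives lies between max(0, (Se + q − 1)/q) and min(1, Se/q), and equals Se if the two tests err independently.

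For Cy-Tb at q = 80%: lower limit (0.758 + 0.80 − 1)/0.80 = 69.8%; upper limit 0.758/0.80 = 94.8%.

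| Assumed q | Denominator of 100 | Cy-Tb (75.8% overall) | Standard F TB (88.9% overall) |
|---|---|---|---|
| 70% | 70 | 65.4–100% | 84.1–100% |
| 80% | 80 | 69.8–94.8% | 86.1–100% |
| 90% | 90 | 73.1–84.2% | 87.7–98.8% |
| 95% | 95 | 74.5–79.8% | 88.3–93.6% |

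**One dataset, two answers.** Suppose 100 patients, 76 Cy-Tb positive, 85 QFT-Plus positive, 72 positive on both (illustrative counts). Over all confirmed patients: 76/100 = 76.0% (Wilson 95% CI 66.8–83.3). Among QFT-Plus positives: 72/85 = 84.7% (75.6–90.8). Independence would put about 0.85 × 76 = 64.6 patients in the overlap, so this example assumes positive association.

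**Precision.** With 90 evaluable patients the Cy-Tb half-width is 1.96 × √(0.758 × 0.242/90) = 0.089. With 72 of them (80%) QFT-Plus positive it is 0.099. Both stay within the planned 0.10.

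**The case against.** The best defence is that the article points to one reading. The Data analysis plan gives an explicit operational definition, the Group 1 sizing agrees with it, and Laboratory procedures separately recognises a microbiological reference standard beside QFT-Plus. The two endpoint entries also follow the order of the objectives: sensitivity in Group 1, then sensitivity and specificity in Groups 2 and 3. On that view only labels are missing, and both analyses can be reported from the same data. This stands as evidence of probable intent. It does not remove the conflict: Objective 1 still says otherwise, the Data analysis plan itself also compares results with QFT-Plus, no sentence says which sensitivity is primary, and the abstract still names a different primary measure.

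Three stronger readings are tempting and are not supported.

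- A reader might infer that a QFT-Plus reference necessarily inflates sensitivity. The limits above allow a lower, unchanged or higher value. A higher value needs positive association. That is plausible, since the Introduction reports Cy-Tb results in line with QFT-Plus, but it is not established.
- A reader might infer that QFT-Plus-negative patients with confirmed TB would be counted as false positives and spoil specificity. Study population assigns only sensitivity to Group 1, so such patients would leave the denominator; no planned Group 1 specificity is affected.
- A reader might infer that any advantage of a new test over QFT-Plus would be hidden. The Data analysis plan also compares the proportion of negative results between the index tests and QFT-Plus, without restricting this to a group, and that would show such a gain in Group 1.

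**Conclusion.** The point holds as an inconsistency in how the primary estimate is defined. Two reference standards are stated for sensitivity in the same patients, and two different sets of primary measures are stated for the study. At an assumed 80% QFT-Plus positivity, a Cy-Tb sensitivity of 75.8% over all patients is compatible with 69.8% to 94.8% against QFT-Plus; at 95% the range narrows to 74.5–79.8%.

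The size depends on QFT-Plus positivity in Group 1 and on how the tests overlap, neither of which the article gives. It also uses the article's planning sensitivities for illustration; according to the Introduction, the 88.9% for Standard F TB came from a comparison with TST, not from confirmed TB patients. The direction of the shift cannot be stated in advance. Precision is adequate under either definition, so the problem is what is being estimated, not how many patients are enrolled.

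**What to change.** 1. In Objective 1, delete the clause naming QFT-Plus as the reference standard.
2. Define Group 1 sensitivity of Cy-Tb, Standard F TB and QFT-Plus over all Xpert Ultra-confirmed participants in that group.
3. Keep Group 3 specificity over all low-risk participants, as the Data analysis plan already has it.
4. Report comparisons with QFT-Plus (Group 2, and any in Groups 1 and 3) separately, labelled as agreement with QFT-Plus.
5. State one primary endpoint in the same words in the abstract and the Endpoints section, naming measure, group and reference, and tie the secondary sensitivity to Group 2 versus QFT-Plus. Whether Group 3 specificity is co-primary or secondary is the sponsor's choice, but the two places must match.

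The cost is wording only; no extra participants, samples or tests are needed. The downside is that the reported Group 1 sensitivities may look less favourable than they would against QFT-Plus.

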## Methods and analysis

### Study design

This diagnostic accuracy study will employ a cross-sectional study design and will be conducted from April 2024 to December 2024.

### Study population

For objective 1, the study will enrol 100 eligible participants with microbiologically confirmed pulmonary TB at the National Lung Hospital, Hanoi, Vietnam for the purpose of verifying the sensitivity of (1) Cy-Tb and (2) Standard F TB for TB infection diagnosis. For objective 2, to evaluate the sensitivity and specificity of the Cy-Tb and Standard F TB tests for TB infection diagnosis, the study will recruit 250 eligible participants, including 200 household contacts of people with pulmonary TB and 50 people with known negative IGRA tests who report no history of exposure to TB.

*Group 1*: people with microbiologically confirmed pulmonary TB. The sensitivity of the Cy-Tb test and Standard F TB assay to diagnose TB infection will be confirmed in this group.

*Group 2*: household contacts of persons with bacteriologically confirmed, pulmonary TB. The sensitivity and specificity of the Cy-Tb test and Standard F TB assay to diagnose TB infection will be verified in this group.

*Group 3*: persons with known negative IGRA tests among those at low risk of TB infection. The specificity of Cy-Tb and Standard F TB for TB infection testing will be estimated using this group.

#### Inclusion criteria

##### All participants

Participants above 18 years of age, able to provide informed consents and have no current plans to relocate outside the designated area for the duration of the study will be included in the study.

###### Group 1 only

People with microbiologically confirmed pulmonary TB disease (either drug-susceptible TB or drug-resistant TB) via Xpert MTB/RIF Ultra (Cepheid, Sunnyvale, California) who also have an abnormal chest X-ray (CXR) result.*

**To reduce the false positive rate of Xpert Ultra assays.*

###### Group 2 only

People without symptoms of active TB disease who are household contacts* of people with new microbiologically confirmed pulmonary TB who initiated treatment in Ha Noi, Vietnam.Have a normal CXR result.

**Household contacts: of a person with TB are defined as members who live under the same roof as the person with contagious pulmonary TB or who meet the following conditions*^4^:

*Sleeping under the same roof or sharing a kitchen space as TB-affected persons at least one night/week for3 monthsbefore the person was diagnosed with TB*.*Staying under the same roof with TB-affected persons for at least1 hour/day and continuously5 days/week for3 monthsbefore the person was diagnosed with TB*.

###### Group 3 only

Known past negative IGRA test results among those at low risk for TB infection.No known and/or reported history of contact or exposure to either TB disease or *M. tuberculosis* bacteria.Have a normal CXR.

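### Group 3, which defines specificity, is entered on a past negative IGRA, so Standard F TB specificity there is conditional on that result and may be overstated

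*Protocol article*

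**What the plan says.** **Entry to group 3.** The Group 3 inclusion criteria require "Known past negative IGRA test results among those at low risk for TB infection", together with no known TB contact and a normal chest X-ray. Study population describes the group as "50 people with known negative IGRA tests who report no history of exposure to TB". Neither place fixes the brand or date of the past test.

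**Use of group 3.** Study population states: "The specificity of Cy-Tb and Standard F TB for TB infection testing will be estimated using this group". The Data analysis plan says: "Specificity is the percentage of participants with negative study tests among those at low risk for TB infection (group 3". That definition mentions low risk but not the past IGRA.

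**Test class.** The Background presents simplified IGRAs as "including the lateral flow Standard F TB assay" and says that it measures interferon-gamma in whole blood after ESAT-6 and CFP-10 stimulation. Cy-Tb injects recombinant forms of the same two antigens and is read on the skin.

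**Other specificity figures.** For group 2, Study population says: "The sensitivity and specificity of the Cy-Tb test and Standard F TB assay to diagnose TB infection will be verified in this group". The Data analysis plan adds the "rate of negative results on the Cy-Tb and Standard F TB tests among QFT-Plus negative participants", and a contingency table against QFT-Plus.

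**Comparisons.** "Differences in proportion of negative results between investigated tests and the reference test will be calculated". Areas under the ROC curve are also planned to compare the two index tests and QFT-Plus.

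**Limitations named.** These are the imperfect sensitivity of QFT-Plus and the single, genetically homogeneous setting. Selection on an earlier IGRA is not among them.

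**The concern.** Specificity counts false positives in people presumed uninfected. If some uninfected people are repeatedly positive on IGRAs, a past negative IGRA keeps them out of the group in which IGRA false positives are to be counted. One index test and the reference are thus pre-screened on their own test class, while the skin test is pre-screened only so far as its reactions track IGRA reactions.

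Two conclusions are at stake. The Standard F TB specificity from group 3 would not carry over to low-risk people without a past IGRA, yet it would be reported without that condition. And a group 3 contrast between Standard F TB (or QFT-Plus) and Cy-Tb would partly reflect the entry rule. The Significance section expects the results to inform guidelines in high-burden countries, so the condition needs to travel with the number.

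**Working it through.** **Inputs from the article (Sample size, Group 3).** Specificity 98.1% for Cy-Tb and 92.5% for Standard F TB; infection 5%; precision 0.1; 95% confidence. Group 3 has 50 people.

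**The plan's own figures.** n = 1.96² × Sp(1 − Sp) / 0.1² / 0.95.
- Cy-Tb: 7.16 / 0.95 = 7.54, so 8.
- Standard F TB: 26.65 / 0.95 = 28.05, so 29.

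Both match the stated 8 and 29, without the 10% drop-out. Dividing by 0.9 as well gives 9 and 32, still below 50, so group size is not the issue.

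**Effect of the entry rule on Standard F TB.** Let f = 1 − 0.925 = 0.075, and let r be the share of these false positives that repeat on any IGRA. The repeatable ones are screened out and the rest occur independently of the past result. Specificity after selection is 1 − (1 − r)f / (1 − rf). The article gives no r, so it is varied:

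| r (assumed) | Specificity in group 3 | Expected false positives in 50 |
|---|---|---|
| 0 | 92.5% | 3.75 |
| 0.25 | 94.3% | 2.87 |
| 0.5 | 96.1% | 1.95 |
| 0.75 | 98.0% | 0.99 |
| 1 | 100% | 0 |

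**A ceiling.** The past test can only remove people on whom it was positive. If it were 97% specific (assumption), then rf ≤ 0.03, so r ≤ 0.03 / 0.075 = 0.4. Specificity is then at most 1 − 0.045 / 0.97 = 95.4%.

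**A second model.** Let φ be the correlation, in uninfected people, between the past IGRA (specificity A) and today's test (specificity T). Then P(negative today | past negative) = T + φ√[A(1 − A)T(1 − T)] / A. With A from 92.5% to 97%:
- Standard F TB stays at 92.5% for φ = 0 and becomes 93.4–94.0% at φ = 0.2, 94.4–95.5% at 0.4 and 95.3–97.0% at 0.6.
- Cy-Tb stays at 98.1% if unrelated to the past IGRA. At half the Standard F TB correlation it reads 98.3–99.3% over the same φ range.
- The Standard F TB minus Cy-Tb difference starts at 92.5 − 98.1 = −5.6 points. For φ from 0.2 to 0.6, with Cy-Tb unrelated or half-correlated, it lies between −4.9 and −1.1, a shift of 0.7 to 4.5 points.

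**When the tilt disappears.** Set all true specificities to 95% and φ = 0.4. An IGRA then reads 97.0%, an unrelated skin test 95.0%, a half-correlated one 96.0% and an equally correlated one 97.0%. With equal true specificity and equal correlation, no advantage remains.

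**Can group 3 reveal the bias?** The Wilson 95% interval is 81.2% to 96.8% for 46/50 and 92.9% to 100% for 50/50. Shifts of a few points lie inside that width.

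**What the rule does legitimately.** Suppose 5% were infected before selection and the past IGRA had sensitivity 88.9% and specificity 92.5% (assumptions). Residual infection is 0.05 × 0.111 / (0.95 × 0.925 + 0.05 × 0.111) = 0.6%. This reduces misclassification for every test.

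**The case against.** Much can be said for the plan. The entry rule is stated openly, and the Data analysis plan calls the rate of negative results a proxy for specificity. With no gold standard in a high-burden country, a past negative IGRA is a sensible screen against hidden infection. All of that stands, and it is why the rule itself need not change. It does not answer the later sentence that defines specificity in group 3 without the condition.

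A reader might infer more than the documents support:

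- *That group 3 is the only source of specificity.* It is not. Study population promises specificity in group 2, which has no past-IGRA criterion, and negatives among QFT-Plus negatives are also planned. The first conflicts with the group 3 definition, since the Data analysis plan gives group 2 only a proportion negative. The second again rests on an IGRA-defined denominator.
- *That inflation is certain.* It requires repeatable false positives, and the range includes no effect. Someone whose false positivity is intermittent or arose after the past test can still enter. The 92.5% also comes from a study with TST as reference (Background), so 7.5% is not a clean IGRA false-positive rate.
- *That every comparison with the skin test favours the IGRAs.* Cy-Tb shares the antigens and may gain too, and group 2 is not selected this way.
- *That the ranking would reverse.* On the plan's values, Standard F TB passes 98.1% only if r exceeds 0.056 / (0.075 − 0.019 × 0.075) = 0.76, even with no gain for Cy-Tb. Selection would mainly narrow the expected gap.

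Finally, the article specifies no group 3 ranking of Cy-Tb against Standard F TB, and the QFT-Plus difference is not tied to group 3. The brand and date of the past IGRA are details that a condensed article may leave to the full protocol.

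**Conclusion.** The point holds in a conditional form. The group that defines specificity is selected on an earlier result of the same test class as one index test and the reference, and neither the definition nor the stated limitations say so. If IGRA false positives repeat within a person, the Standard F TB figure is too high for low-risk people without a past IGRA. At the plan's 92.5%, the overstatement is 0 points if none repeat, 1.8 if a quarter do and 3.6 if half do, with a ceiling of about 2.9 if the past IGRA were 97% specific. The correlation model gives 0.9 to 4.5 points for φ of 0.2 to 0.6. Group 3 contrasts with Cy-Tb move toward the IGRAs by up to a similar amount, and by less the more closely Cy-Tb follows the past IGRA. Repeatability, φ and the past test's specificity are all assumptions. This is a fault of labelling and permitted inference; it does not invalidate the entry rule.

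**What to change.** Keep the entry criterion and change the Data analysis plan as follows:

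1. Define and report the group 3 result as *specificity conditional on a past negative IGRA*.
2. State that Cy-Tb will not be ranked against Standard F TB or QFT-Plus on specificity from group 3.
3. Report any group 3 difference from QFT-Plus only under that label, with the discordant counts (skin test positive with IGRA negative, and the reverse).
4. Add the selection on a past IGRA to the limitations, with its likely direction.
5. Reconcile the group 3 definition of specificity with the group 2 specificity promised under Study population, saying which estimate comes from which group and against which standard.

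The cost is wording and one small table. Recruitment, sample size and testing are unchanged. The price is a narrower specificity claim.
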